**Figure 2 F2:**
[figure not shown]
Pre-intervention and post-intervention periods for objectives 1–4 of the OPEN Stewardship Study. (A) Objective 1, overall prescribing (report sent at *t_0_*). (B) Objective 2, prescribing with duration longer than 7 days (report sent at *t_0_*). (C) Objective 3, prescribing for viral respiratory conditions (report sent at *t_3_*). (D) Objective 4, prescribing for acute sinusitis (report sent at *t_6_*). *t_0_* represents the time of the first report (intervention); *t_−12_* represents 1 year prior to the first report; *t_12_* marks the conclusion of the study period (1 year after the first report).

**Table 3 T3:** Timing of analyses for objectives 1–4 of the study

Objective	Outcome	Unit of analysis	Intervention time	Number of observations in intervention cohort		Total observations/observations in control cohort
				Pre-intervention	Post-intervention	
1	Prescribing for all indications	Provider	*t_0_*	12	12	24
2	Prescribing (for all indications) with duration longer than 7 days	Provider	*t_0_*	12	12	24
3	Prescribing for viral respiratory conditions	Provider	*t_3_*	15	9	24
4	Prescribing for acute sinusitis	Provider	*t_6_*	18	6	24

The definitions of the pre-intervention and post-intervention periods are dependent on the delivery time of the report (intervention) related to each objective.

The intervention effect will be modelled as a level change and/or change in slope for the prescribing rate at the beginning of the post-intervention period.^26^ An interaction term with study site will be included to allow for differences in the intervention effect between Ontario and Southern Israel. A key assumption of interrupted time-series analysis is that the pre-intervention time trend is assumed to be linear, which must be evaluated through visualisation.^34^ Otherwise, non-linear terms may be considered. Model fit can be assessed by comparing models containing intervention parameters to a null model not containing intervention parameters using a statistic such as Akaike information criterion.

Autocorrelation in each provider’s time-series should be accounted for by the random intercept (provider nested within practice group nested within study site) and by controlling for seasonality (categorical variable for month).^26^ In case autocorrelation is present in the residual distribution, an autoregressive covariance structure will be considered.

Stewardship interventions often result in a reversion to baseline behaviour after the intervention is discontinued.^35 36^ To examine the durability of the intervention effect, we will contrast the coefficients estimated from models including (1) all months in the post-intervention period, (2) the first 3 months in the post-intervention period, (3) the first 6 months in the post-intervention period. Finally, since the first report at *t_0_* (highlighting overall prescribing) is likely to affect objectives targeted by later reports (at *t_3_* or *t_6_*), for objectives 3 and 4, we will consider *t_0_* as an alternative start time of the post-intervention period.

As the COVID-19 pandemic represents a major disruption of primary care, its effect on prescribing will be modelled as one or more separate ‘intervention points’ in the time-series analysis.

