#### Covariates

The analysis will include potential predictors of a provider’s baseline prescribing rate, as well as seasonality (table 2). These include a provider’s age, sex and employment status (full-time or part-time),^10^ and monthly practice patient composition (by age and sex).^19 32^ We will also use nested random intercepts for provider, practice group (clinic) and study site, representing within-group prescribing norms and a provider’s baseline willingness to prescribe after accounting for other predictors, as well as heterogeneity between study sites. Seasonality will be accounted for using a categorical variable for each month compared with January. An interaction term with study site will be included for each covariate to allow for differences in seasonal and demographic prescribing patterns between the two countries in our study.

**Table 2 T2:** Covariates included in the interrupted time-series analysis of the OPEN Stewardship Study

Variable	Purpose	Form	Description
Number of prescriptions	Outcome	Integer	Number of antimicrobial prescriptions for given indication
Number of visits for indication	Offset	Integer	Number of patient visits for given indication
Study site	Covariate	Binary	Southern Israel versus Ontario, Canada (baseline)
Practice group	Random intercept	ID	Random intercept for practice group (nested within region)
Provider	Random intercept	ID	Random intercept for provider (nested within practice group)
Month	Covariate	Categorical	Calendar month (baseline=January)
Month×study site	Interaction	Interaction	Allows different value for coefficients for Southern Israel
Physician age	Covariate	Integer	Physician age at *t_−12_*
Physician age×study site	Interaction	Interaction	Allows different value for coefficient for Southern Israel
Physician sex	Covariate	Binary	Female versus male (baseline)
Physician sex×study site	Interaction	Interaction	Allows different value for coefficient for Southern Israel
Physician employment status	Covariate	Binary	Part-time versus full-time (baseline)
Physician employment status×study site	Interaction	Interaction	Allows different value for coefficient for Southern Israel
Percent female patients	Covariate	Continuous	Percentage of visits by female patients
Percent female patients×study site	Interaction	Interaction	Allows different value for coefficient for Southern Israel
Percent patients 17 and under	Covariate	Continuous	Percentage of visits by patients 17 and younger

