Percent patients 17 and under×study site	Interaction	Interaction	Allows different value for coefficient for Southern Israel
Percent patients 65 and older	Covariate	Continuous	Percentage of visits by patients 65 and older
Percent patients 65 and older×study site	Interaction	Interaction	Allows different value for coefficient for Southern Israel
Post-intervention	Intervention	Binary	1 if provider is in intervention group and intervention has occurred, 0 otherwise; level change of the outcome associated with intervention
Post-intervention×study site	Interaction	Interaction	Allows different value for level change of the outcome for Southern Israel
Time	Trend	Integer	Time since the beginning of the study; slope of the time trend of the outcome
Time×study site	Interaction	Interaction	Allows different value for slope of the time trend of the outcome for Southern Israel
Time×post-intervention	Intervention effect	Interaction	Change in slope of time trend in the intervention group after intervention is received
Time×post-intervention×study site	Interaction	Interaction	Allows different value for change in slope of time trend in the intervention group after intervention is received for Southern Israel

Excludes variables related to the effect of the COVID-19 pandemic.

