#### Statistical analysis

We will perform a multilevel, controlled interrupted time-series analysis with the provider as the unit of analysis.^33^ A negative binomial model (to allow for overdispersion of the outcome) will be used with prescribing rates as the outcome. Each provider in the intervention group will contribute 24 observations: a minimum of 12 months in the pre-intervention period (*t_−12_* to *t_0_*) and up to 12 months in the post-intervention period, depending on the objective. The pre-intervention and post-intervention periods of each outcome are defined by the time when the relevant report was delivered. The first report (*t_0_*) corresponds to objectives 1 and 2, the second report (*t_3_*) to objective 3 and the third report (*t_6_*) to objective 4. The pre-intervention and post-intervention periods of each objective are summarised in table 3. Providers in the external control group will contribute 24 observations in the control period. The timeline of the study for each objective is shown in figure 2.

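### The intercept-only model captures neither decaying correlation nor provider differences in pre-to-post change, so intervention standard errors can be too small by an amount the article's figures cannot fix

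*Protocol article*

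**What the plan says.** Under Covariates the article states: "We will also use nested random intercepts for provider, practice group (clinic) and study site". Table 2 lists the provider term as "Random intercept for provider (nested within practice group"), and no random effect other than an intercept appears.

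The two intervention rows of Table 2 are fixed effects. The level term is "1 if provider is in intervention group and intervention has occurred, 0 otherwise; level change of the outcome associated with intervention"; the slope term is "Change in slope of time trend in the intervention group after intervention is received". Each has an interaction with study site, but neither varies by provider.

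The Statistical analysis section (text after Table 3) then says that autocorrelation in each provider's "time-series should be accounted for by the random intercept (provider nested within practice group nested within study site"), together with the categorical month variable. The fallback follows: "In case autocorrelation is present in the residual distribution, an autoregressive covariance structure will be considered". On the outcome distribution: "A negative binomial model (to allow for overdispersion of the outcome) will be used with prescribing rates as the outcome". The article mentions no clustered or robust standard error.

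Separately, the Covariates text gives study site a random intercept, while Table 2 enters site as a fixed binary covariate, "Southern Israel versus Ontario, Canada (baseline").

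**The concern.** The stated premise is wrong as a matter of statistics. A provider intercept implies one common correlation between any two of that provider's months, whether adjacent or 23 months apart. Month terms remove the seasonal pattern shared within a site. The negative binomial dispersion covers extra variation that is independent from month to month. None of these represents correlation that decays with lag, or providers whose rates shift by different amounts over the study.

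The second gap matters because exposure switches on within provider. The relevant error for the level change is therefore how much providers differ in their own pre-to-post change, and the model sets that variance to zero. Given the intercept, it treats a provider's 12 post-intervention months as independent evidence. Different shifts are plausible here, since the article itself describes the pandemic as a large disruption of primary care during the study. At stake are intervals that are too narrow and P values that are too small for the level change.

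**Working it through.** **The plan's own figure.** The article gives no standard error, autocorrelation or error rate for the time-series model. Its one computed figure is about 15 physicians per group. It reproduces: (1.645 + 1.282)² × (1/0.126 + 1/0.107) / ln(0.126/0.107)² = 5,540 visits per group, and 5,540/368 = 15.05. That is an independent-Poisson calculation and says nothing about the error rate of the planned model.

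**Inputs from the article.** 50 intervention and about 350 control providers (Ontario, Participants); 24 months, 12 before and 12 after (Table 3, objectives 1–2); 0.126 prescriptions per visit and 368 visits per month (Sample size).

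**Assumptions.** Residual variance 0.072 on the log-rate scale: sampling variance 1/(368 × 0.126) = 0.022 plus about 0.05 for month-level overdispersion. Provider SD of pre-to-post change s = 5–20%, in both groups. Time is centred at the switch. Tests are two-sided at 5% with no true effect.

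**Level-only model, by hand.**
- Variance of one provider's pre-to-post difference: 0.072 × (1/12 + 1/12) = 0.012.
- Group factor: 1/50 + 1/350 = 0.02286.
- Model standard error with no heterogeneity: √(0.012 × 0.02286) = 0.0166.
- True standard error with heterogeneity: √((0.012 + s²) × 0.02286).
- The fitted model absorbs a little of s² into its residual variance, which becomes 0.072 + s² × 6/23 (6 = 12 × 12/24; 23 = 24 − 1).
- Rejection rate: 2 × [1 − Φ(1.96 × model SE / true SE)].

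For s = 10%, the residual is 0.0746, the model SE 0.0169, the true SE 0.0224, the ratio 1.33 and the rejection rate 14%.

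**Full random-intercept fit.** The last three columns use generalised least squares with month and time terms.

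| s | Model SE (hand) | True SE (hand) | Rejection (hand) | Level-only fit | Both Table 2 terms: level | Both: slope |
|---|---|---|---|---|---|---|
| 5% | 0.0166 | 0.0182 | 7% | 7% | 6% | 5% |
| 10% | 0.0169 | 0.0224 | 14% | 14% | 9% | 5% |
| 15% | 0.0172 | 0.0281 | 23% | 24% | 14% | 4% |
| 20% | 0.0177 | 0.0345 | 31% | 32% | 19% | 4% |

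With both terms, the level is estimated at the switch point alongside a slope. Its sampling error is larger, so ignored heterogeneity is a smaller share of the total.

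**Other departures, same residual variance.**
- Provider trends with SD 1% or 1.5% per month: 17% or 27% level-only, but only 6–8% for either term when both are fitted.
- First-order autoregressive correlation of 0.4 without the fallback: 18% level-only, 16% for each term when both are fitted.

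**Sensitivity to the residual variance.** With sampling variance alone (0.022), s = 5–20% gives 13–50% level-only and 8–34% for the level term with both fitted.

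**Does the fallback repair it?** In the 0.022 setting, level-only, fitting the autoregressive structure returns the error rate to 5.0% when that correlation is the only problem. With provider change SD of 5%, 10% and 20% it still leaves 8.0%, 15.2% and 29.3%.

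**Sparse outcomes.** With an assumed 2.5 prescriptions per month and 18 months before v 6 after (the objective 4 split), the level-only rate is 5.5–11.5%.

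**Does the remedy work?** In 500 simulated count datasets per scenario, provider-clustered standard errors gave 4.8–7.6%. The Monte Carlo error is about √(0.05 × 0.95/500) = 1 percentage point.

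**The case against.** The strongest reply is that the plan anticipates residual autocorrelation and provides an autoregressive structure for it. That reply stands for pure autoregressive correlation: if the structure is fitted, the test is restored. It does not stand for provider-specific change, which the structure does not represent. The step is also only to be considered, with no stated trigger.

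A second reply is that an article condenses its plan, and robust variances may be specified elsewhere. That would excuse silence. Here, however, the article lists the random effects and asserts that the intercept should suffice, and that assertion is incorrect.

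A reader might go further and infer that false-positive rates will be several times nominal for all four objectives. The article does not support this, for four reasons:
- Every variance involved is assumed, including the residual variance of 0.072. At a change SD of 5% the rate is only 6–7%.
- The largest rates belong to a level-only model. The article allows a step, a slope change or both, and Table 2 lists both terms. Fitting both roughly halves the excess from step heterogeneity and nearly removes that from provider trends.
- The slope-change term is not inflated by differing step changes.
- Objectives 3 and 4 rest on fewer events, so sampling noise dominates and inflation should be smaller.

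The conflict over study site is real but minor. A site variance from two sites cannot usefully be estimated beside a fixed site effect, but no effect on the intervention standard errors has been shown.

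**Conclusion.** The concern holds in a limited form. The premise that nested intercepts and month terms account for autocorrelation is wrong, and the tabulated model has no provider-level variance for the intervention terms. Standard errors for the level change can be too small. For overall prescribing, under the assumptions above (residual variance 0.072, change SD 5–20%), a nominal 5% test runs at about 7–32% level-only and about 6–19% with both Table 2 terms. Unmodelled first-order autoregressive correlation of 0.4 gives about 16–18%. A smaller residual variance would raise these rates and a smaller change SD would lower them. The article fixes neither, so the size in this trial is unknown until it is estimated from pre-intervention data. The mechanism is certain; the magnitude is conditional.

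**What to change.** - Take standard errors and intervals for the intervention terms from a provider- or clinic-level cluster-robust variance or cluster bootstrap. Alternatively, add provider-level random effects for time and for pre-to-post change.
- If the random-change route is chosen, define a calendar switch month for controls. Table 2 codes them 0 throughout and Ontario participants start in at least two waves, so none exists at present.
- Replace the conditional autoregressive step with a fixed rule: either always fit it, or state the test and threshold that trigger it.
- As a separate tidy-up, reconcile the Covariates text and the nesting description with Table 2 by keeping study site as a fixed effect only.

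The cost is a few sentences and some computing time. The intervals will be wider, and the random-effects version may need convergence work, for which the cluster bootstrap is a ready substitute.

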#### Intervention

The intervention will consist of three personalised reports generated by the OPEN Stewardship platform and emailed to participants in the intervention group. The first report will be sent at the beginning of the intervention period (*t_0_*) and will consist of a welcome email followed by a benchmark of the provider’s overall antimicrobial prescribing rate relative to the average and 25th percentile of participants in the same network (UTOPIAN or CHS) during the previous year (2019). This report will also include guidelines highlighting that most conditions do not require more than 7 days of antimicrobials and a benchmark of the provider’s proportion of antimicrobial prescriptions with duration longer than 7 days relative to the average and 25th percentile of participants in the same network during the previous year. We chose to benchmark against other participants only (excluding non-participants) due to the expectation that those self-selecting into a stewardship intervention may already have lower rates of prescribing.

The two subsequent reports will be sent 3 (*t_3_*) and 6 (*t_6_*) months after the first report. These reports will target viral respiratory conditions (as defined by the primary International Classification of Diseases, Ninth Revision (ICD-9) code associated with the visit, see online supplemental table S1) and acute sinusitis, respectively, and will consist of a benchmark of the provider’s prescribing for the specified indication as well as site-specific best practice guidelines for the specified indication. The study concludes 1 year after the first report is sent (*t_12_*). The composition of each report is summarised in table 1. An example figure is shown in figure 1.

10.1136/bmjopen-2020-039810.supp1Supplementary data

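### The durability analysis contrasts nested post-intervention windows, so no window isolates the late months, and one of its comparisons is void for objective 4

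*Protocol article*

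**What the plan says.** The Statistical analysis section of the protocol article gives the reason for the durability analysis: "Stewardship interventions often result in a reversion to baseline behaviour after the intervention is discontinued". It then sets the method: "contrast the coefficients estimated from models including (1) all months in the post-intervention period, (2) the first 3 months", and "3) the first 6 months in the post-intervention period". It does not say which coefficient is contrasted. The same section allows the intervention effect to be a level change, a slope change or both, and Table 2 lists a time by post-intervention term.

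Table 3 fixes the length of each post-intervention period. Objective 1 reads "Prescribing for all indications Provider *t_0_* 12 12 24" (12 months before, 12 after), and objective 2 has the same split. Objective 3 reads "Prescribing for viral respiratory conditions Provider *t_3_* 15 9 24" (15 and 9). Objective 4, "prescribing for acute sinusitis", has 18 and 6.

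On report timing, the Intervention section says: "The two subsequent reports will be sent 3 (*t_3_*) and 6 (*t_6_*) months after the first report". Follow-up ends at t12. For objectives 3 and 4, t0 is also considered as an alternative start of the post-intervention period.

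**The concern.** Reversion is a difference between early and late months. The three windows all begin at the start of the post-intervention period and differ only in where they stop. The longest one mixes late months with early ones, and no window holds late months alone. A contrast between such windows therefore sees the late effect only after it has been pooled with the early effect.

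For objectives 1-2 this means that t6 to t12, the period after the last report is sent, is never estimated separately. The first-6-months window, t0 to t6, is the phase in which reports are still going out.

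At stake is the durability conclusion, not the main effect estimates. A reader given these contrasts could believe that a good part of the effect persists when it has gone, or see no change across windows when the effect has faded steadily.

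**Working it through.** The plan attaches no figure to the durability analysis, so there is none to reproduce. The Table 3 month counts are consistent: 12 + 12, 15 + 9 and 18 + 6 all equal 24.

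**Step 1. Month counts for objective 4.** The post-intervention period is 6 months. All months = first 6 months, so the two models use identical data and their contrast is exactly 0. All 6 against the first 3 is still a real comparison.

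**Step 2. Dilution by simple averaging.** Let P be the post-intervention months, k the short window, E the mean log rate ratio in months 1 to k, and L the mean in months k+1 to P.

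All-months mean = (k·E + (P − k)·L)/P, so

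(all − first k) = ((P − k)/P) × (L − E).

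Share of the early-late difference that the contrast keeps:

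| Objective | P | All v first 3 | All v first 6 |
|---|---|---|---|
| 1, 2 | 12 | 9/12 = 75% | 6/12 = 50% |
| 3 | 9 | 6/9 = 67% | 3/9 = 33% |
| 4 | 6 | 3/6 = 50% | 0/6 = 0% |

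**Step 3. Level-only controlled time-series, objective 1.** The model is noiseless least squares on the log rate, with group, common linear trend and post-intervention level. The assumed truth is a rate ratio of 0.85 (the 15% reduction in the Sample size section; ln 0.85 = −0.1625) in months 1-6 and no effect in months 7-12. The true late-minus-early difference is 0 − (−0.1625) = 0.1625.

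- First 6 months: −0.1625, rate ratio 0.85.
- All 12 months, the two groups weighted equally: −0.1057, rate ratio 0.90.
- Contrast: 0.1625 − 0.1057 = 0.0568, and 0.0568/0.1625 = 35%.

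The share is below 50% because the shared trend takes up some of the rise. More controls pin that trend. I refitted with control series weighted by the planned numbers:

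- Ontario, 350 to 50 (7:1): all-months coefficient −0.0855 (rate ratio 0.92), share 47%.
- Southern Israel, 250-300 to 50-100 (2.5:1 to 6:1): share 43% to 47%.

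The ceiling is the 50% of step 2.

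**Step 4. Adding a slope term, objective 1**, with post-intervention time counted from the start of the post period.

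- Linear fade from 0.85 in month 1 to no effect in month 12: level −0.1625 and slope +0.0148 per month in all three windows. The cross-window contrast is 0 although reversion is complete; the slope itself shows it.
- Effect for 6 months, then none: first 6 gives level −0.1625, slope 0; all 12 gives level −0.194, slope +0.0205. The level alone suggests a stronger effect over the longer window. Level and slope together give −0.194 + 11 × 0.0205 = +0.03 at month 12, a rate ratio of about 1.03, so the loss is visible there.

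**Step 5. Disjoint windows, same truth.** Months 1-6 = −0.1625, months 7-12 = 0, difference 0.1625: the full reversion.

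**The case against.** The strongest reply is the slope term. The plan permits it, and a positive post-intervention slope after an initial drop is evidence of reversion. A reader might infer that the plan cannot answer its durability question at all, or that complete loss must appear as partial retention. The documents do not support that: it holds only if a level change alone is fitted. What stands is that the stated procedure is to compare coefficients across windows, and step 4 shows that this comparison can be null or misdirected even when the slope within one model is informative.

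A reader might also call the objective 4 analysis wholly degenerate. It is not: one comparison is void, and all 6 against the first 3 survives with later months at half weight. The alternative t0 start gives 12 post-intervention months and three distinct windows, but for objective 4 the first 3 and first 6 of those months would precede the sinusitis report at t6, so they cannot show reversion from it.

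Nor does overlap rule out a valid test. Correlated estimates can be compared using their covariance or a cluster bootstrap, and the protocol promises a contrast, not a test.

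A loss of season-trend separation through truncation might also be inferred. It is weak: at 18 months half the calendar months still repeat, objectives 3 and 4 keep at least 18 months, and nothing says that the controls are truncated.

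Two further replies have some force. The t3 and t6 reports target other indications, so calling t0 to t6 active intervention for objectives 1-2 is approximate, and t6 to t12 begins with delivery of a report. The choice of coefficient and test may also sit in an analysis plan not shown here. The windows themselves, however, are fixed in the protocol.

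**Conclusion.** The point stands as a defect in a secondary analysis. From the text and Table 3 alone, the windows are nested, no window isolates late months, and one objective 4 contrast is zero by construction. The dilution figures in step 2 apply when a mean level change is contrasted. The 35% in step 3 also assumes an initial rate ratio of 0.85, abrupt loss at month 6 and equally weighted groups; at the planned group ratios the share is 43% to 47%. With a slope term there is no fixed direction of error: the slope can reveal reversion, but the planned cross-window contrast need not. The decay patterns are assumptions; the month counts are not. The main effect estimates are unaffected.

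**What to change.** Replace the three nested fits with one model per objective on all 24 months, using mutually exclusive post-period indicators:

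- objectives 1-2: months 1-3, 4-6, 7-12;
- objective 3: months 1-3, 4-6, 7-9;
- objective 4: months 1-3, 4-6.

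Report late minus early with its confidence interval from that model. For objectives 1-2, name t6-t12 against t0-t6 as the durability contrast, and state that the later period starts when the third report is delivered.

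The cost is a few added parameters and somewhat less precise late-window estimates. No new data are needed, and the change is one of wording and model specification.

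### Repeating month effects, one straight line and COVID-19 points describe the time course shared with controls, so shared changes that they miss can leak into the intervention terms, mainly for objectives 3 and 4

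*Protocol article*

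**What the plan says.** Four statements in the Protocol article fix the time structure of the model.

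- **Season** (Covariates): "Seasonality will be accounted for using a categorical variable for each month compared with January". Table 2 interacts month with site ("Allows different value for coefficients for Southern Israel"), so each site has one monthly pattern that repeats in both years.
- **Trend** (Table 2): one integer Time term, described as "Time since the beginning of the study; slope of the time trend of the outcome", also interacted with site. The Statistical analysis section has the linearity of the pre-intervention trend checked by eye. It adds: "Otherwise, non-linear terms may be considered".
- **COVID-19** (last paragraph of Statistical analysis): "As the COVID-19 pandemic represents a major disruption of primary care, its effect on prescribing will be modelled as one or more separate" intervention points. The footnote to Table 2 reads "Excludes variables related to the effect of the COVID-19 pandemic".
- **Intervention** (Table 2): Post-intervention equals 1 only for participants after the report. Time×post-intervention is the matching slope change. Table 2 lists no post-period term common to both groups.

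The effect starts at month 12 of 24 for objectives 1–2, month 15 for objective 3 and month 18 for objective 4 (Table 3). Ontario starts in at least two waves. The first report benchmarks prescribing "during the previous year (2019"), which places t0 in 2020. About 350 Ontario and 250–300 Israeli non-participants supply 24 monthly observations each.

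**The concern.** A 24-month window around a 2020 start joins ordinary and pandemic months. Repeating month effects cannot represent a season that differs between the two years, and a COVID-19 level shift cannot either. A straight line cannot represent a fall followed by recovery. Shared movement that these forms miss stays in the residuals of both groups. The only remaining terms that vary over the later months are the participants' level and slope, so part of the misfit is attributed to them.

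At stake is the purpose of the control group. A change that affected participants and controls alike could be reported in part as an effect of the reports, with a sign and size that depend on the start month and on where the COVID-19 points are placed. Concurrent controls at the same site allow the shared course to be estimated month by month, so the parametric forms are not needed.

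**Working it through.** **1. Inputs.** From the article: 50 participants and about 350 controls in Ontario, 24 months, effect starts at months 12, 15 and 18, and a planning effect of 15% (0.126 to 0.107 per visit, Sample size). The documents give no seasonal amplitude or pandemic effect, so these are assumed: log-rate season log(1.2)·cos with a January peak, absent from March 2020; a level drop of log(0.8) from March 2020; t0 in any month of 2020; no true effect; and the same shock r(t) in both groups.

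**2. When a shared shock leaks.** Use least squares on the log rate with provider intercepts removed, as a linear stand-in for the negative binomial model. Let g be the share of participants, P the post indicator over the 24 months, P̃ its centred form, and e the part of P not explained by the common terms (month, Time, COVID-19 step). For a level-only effect the bias is

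b = e′r / [(1 − g)·P̃′P̃ + g·e′e].

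If the common terms reproduce P, then e = 0 and there is no leak.

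- Start at month 12: I(t ≥ 12) = (t − t mod 12)/12, a line minus a repeating month pattern. Hence e = 0 and b = 0 whatever the shared shock.
- Starts at months 15 and 18: relative to centred P, the residual after month and Time is 0.45 and 0.58. The protection is lost.
- Example, objective 4, t0 in April 2020, g = 50/400 = 0.125: e′r = −0.3154, P̃′P̃ = 4.5, e′e = 1.3636. Then b = −0.3154/(0.875 × 4.5 + 0.125 × 1.3636) = −0.3154/4.108 = −0.0768, a false change of −7.4%.

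**3. Level and slope model**, range over t0 = January to December 2020, slope centred at the report month:

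| Scenario | Quantity | Obj 1–2 | Obj 3 | Obj 4 |
|---|---|---|---|---|
| One correctly dated COVID-19 step | level | 0 to +7.9% | −6.8 to +11.9% | −11.1 to +9.9% |
| Same | post-period average | 0% | −4.8 to +1.3% | −7.4 to 0% |
| Swing halved (20% peak to trough) | level | 0 to +3.9% | −3.5 to +5.8% | −5.7 to +4.8% |
| One COVID-19 point, level and slope | level | 0% | −1.5 to +10.1% | −2.9 to +10.0% |
| Two such points, 3 months apart | level | 0% | −1.5 to +1.5% | −2.4 to +2.7% |
| Per-visit season unchanged | level | 0% | 0% | 0% |
| Month-year indicators | level | 0% | 0% | 0% |

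The full swing of ±log 1.2 is 1.2² = 1.44, or 44% from trough to peak. A level-only intervention model gives the same ranges as the average row.

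**4. A second assumed shock.** Prescribing falls 30%, recovers to −15% over 8 months and loses its season, with onset at month 10 or 14. Noise-free Poisson fits for Ontario with one correctly dated step give these false level ratios:

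| Model | Obj 1–2 | Obj 3 | Obj 4 |
|---|---|---|---|
| Level and slope | 0.907 or 0.986 | 1.105 or 1.044 | 1.162 or 1.128 |
| Level only | 1.000 | 1.084 or 1.025 | 1.077 or 1.031 |

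The average bias for objectives 3–4 is now upward where step 3 gave mostly downward values, so the sign is not predictable. For objectives 1–2 with the slope term, the post-period average stays at 0.99–1.00. With waves starting at months 12 and 14 and onset at month 10, a level-only model for objectives 1–2 gives a ratio of 1.03. Its simulated false-positive rate is 36% at a nominal 5% (300 data sets, 368 visits per provider-month). Month-year indicators give 1.000 without noise and 2–8% false positives across the simulated cases.

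**The case against.** The case against is substantial, and most of it limits the size of the problem.

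- **The article does not say that a COVID-19 point is a step.** It models its own intervention as a level change, a slope change or both. Read that way, the level bias is 0% for objectives 1–2, and two such points nearly remove it for objectives 3–4. This stands, but the second result depends on the number and placement of the points.
- **Outcomes 3 and 4 are rates per visit for the indication.** A missing respiratory season removes visits as well as prescriptions. If prescribing per visit keeps its seasonal pattern, nothing leaks. This stands: the documents do not show whether that pattern changed.
- **Unstated number and dates of COVID-19 points.** A condensed article may leave these to the analysis plan, and they are no fault here. A reader might infer that the points will be chosen by hand after seeing the data; the text does not say so. The point concerns the structure in Table 2.
- **Optional non-linear terms.** They are tied to viewing the pre-intervention trend, so they do not deal with a season that changes afterwards.

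Two stronger readings are tempting. One is that overall and long-course prescribing would show a false average effect. With one common start they would not. The other is a spurious effect of about −17%. That figure needs a separate time slope for participants, which Table 2 does not contain, so it should not be set against the 15% planning effect.

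**Conclusion.** The concern holds in a limited form. Under the tabled structure, a change shared by participants and controls can enter the intervention coefficients when season, line and COVID-19 points do not describe it. This mainly affects objectives 3 and 4 and Ontario's staggered waves. For objectives 1–2 with a single start the average effect is protected. What can arise is a false drop and rebound, or the reverse, which matters because the plan contrasts the first 3 and 6 months with the whole post-period to judge durability.

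Under the larger assumed swing and one step, the average bias reaches about −5% for objective 3 and −7% for objective 4. The latter is about half of 15%, an effect that the article sets for overall prescribing and not for these outcomes. Shock shape, seasonal amplitude and start month are all assumptions, and plausible alternatives take the bias to zero. The simulated false-positive rates use all-visit volume and would overstate significance for objectives 3–4; the bias itself does not depend on volume. This is a worthwhile change to the primary model, not evidence that the planned result must be wrong.

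**What to change.** In the primary model, replace the month-of-year categories, linear Time and COVID-19 points with one indicator for each calendar month and year within each site, shared by participants and controls. The intervention level and slope then measure departures from concurrent controls at the same site. Index the indicators by actual calendar month so that Ontario's waves align, with control data for every month in which any wave contributes. Keep the trend, season and COVID-19-point model as a sensitivity analysis.

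The cost is small: 24 months need 23 contrasts per site, against 11 + 1 + 1 = 13 with one COVID-19 step, so about 10 more parameters per site. A common trend would no longer be reported as a single slope. The change removes shared shocks that are equal on the log scale and the dependence on where COVID-19 points are placed. It does not remove shocks that affect volunteers differently, and the report should say so.
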